## Abstract

**Background:**

Medication-related problems are a serious concern in Australian primary care. Pharmacist interventions have been shown to be effective in identifying and resolving these problems. Collaborative general practitioner-pharmacist services currently available in Australia are limited and underused. Limitations include geographical isolation of pharmacists and lack of communication and access to patient information. Co-location of pharmacists within the general practice clinics is a possible solution. There have been no studies in the Australian setting exploring the role of pharmacists within general practice clinics.

The aim of this study is to develop and test a multifaceted practice pharmacist role in primary care practices to improve the quality use of medicines by patients and clinic staff.

**Methods/design:**

This is a multi-centre, prospective intervention study with a pre-post design and a qualitative component. A practice pharmacist will be located in each of two clinics and provide short and long patient consultations, drug information services and quality assurance activities. Patients receiving long consultation with a pharmacist will be followed up at 3 and 6 months. Based on sample size calculations, at least 50 patients will be recruited for long patient consultations across both sites. Outcome measures include the number, type and severity of medication-related problems identified and resolved; medication adherence; and patient satisfaction. Brief structured interviews will be conducted with patients participating in the study to evaluate their experiences with the service. Staff collaboration and satisfaction with the service will be assessed.

**Discussion:**

This intervention has the potential to optimise medication use in primary care clinics leading to better health outcomes. This study will provide data about the effectiveness of the proposed model for pharmacist involvement in Australian general practice clinics, that will be useful to guide further research and development in this area.

**Trial registration:**

Australian New Zealand Clinical Trials Registry: ACTRN12612000742875

## Background

Medication misadventure remains a serious concern in Australian primary care [1,2]. It is estimated that one in 10 patients who visit their general practitioner (GP) experience a medication-related problem (MRP), of which almost half are considered moderate or severe, with 8% requiring hospitalization [1]. Approximately one in four of these are preventable. These data are consistent with studies from other countries. For example, a recent UK study revealed that one in 20 prescription items in general practice contained an error, affecting 1 in 8 patients [3]. Poor communication has been identified as a major contributing factor towards MRPs, [2] highlighting the need for greater collaboration between GPs, pharmacists and other primary health professionals to ensure optimal patient care.

Collaborative medication reviews, undertaken by pharmacists and GPs, have been successful in identifying and resolving medication-related problems, improving quality of prescribing, and optimizing drug use and costs [4,5]. These collaborative services, however, are currently limited and underused due to factors including geographical isolation, limited access to patient medical records, a lack of time for team activities and a health policy that is not conducive to such collaborative arrangements [6]. Additionally, communication between GPs and pharmacists in the community setting is sporadic and reactive, risking fragmentation of patient care [7].

A possible solution to these problems is the integration of pharmacists into general practices and primary healthcare clinics. In countries such as the United Kingdom, Canada and the United States, practice pharmacists work in close collaboration with GPs (family physicians) to undertake a range of clinical and administrative tasks [8,9]. Some studies suggest the implementation of these roles can result in improved medication use and health outcomes and reduced health service use and cost [10-12]. Co-location has also been shown to enable greater communication and cooperation between health professionals, and strengthen the primary health care team [13].

The aim of this study is to develop and test a multifaceted practice pharmacist role in primary care practices in Australia to improve the quality use of medicines by patients and clinic staff.

## Methods/design

This is a multi-centre, prospective intervention study with a pre-post design and a qualitative component, involving two general practice (primary care) clinics in Melbourne, Australia.

### Recruitment of practices and pharmacists

Primary care clinics will be invited to participate through advertisements and consultation with the Victorian Divisions of General Practice and key informants in Melbourne, Australia. Primary care practices that have the space to accommodate a co-located pharmacist will be targeted. An independent practice pharmacist with significant clinical experience and accreditation to conduct Government funded collaborative Home Medicines Reviews (HMRs) will be identified for each clinic through advertisements and key informants.

### Intervention

The intervention will consist of a multi-faceted, collaborative service targeting patients and practice staff. A practice pharmacist will be co-located in each of the study clinics for at least eight hours per week for six months. The practice pharmacist will undertake the following tasks:

1. Long patient consultations

2. Short patient consultations

3. Drug information and education service for clinic staff; and

4. Quality assurance activities

### Long patient consultation

#### Recruitment of participants

Participants for the long patient consultations will be practice patients who may be at an increased risk of MRPs [14].

#### Inclusion criteria

• Using five or more medicines

• Using one or more medicines that require therapeutic drug monitoring (e.g. warfarin, phenytoin, lithium)

• Using medicines for three or more medical problems

• Have had a recent unplanned hospital admission/emergency department visit

• Having other reason(s) for being at risk of medication misadventure (e.g. adherence issues, language barriers, multiple prescribers)

#### Exclusion criteria

• Have had a HMR in the previous 12 months with no subsequent significant change in clinical status or medication regimen

• Are unable to provide written informed consent

• Are under 18 years of age

• Are unavailable for follow up for six months after recruitment

Patients meeting one or more of the eligibility criteria will be considered for referral to the study by their general practitioner or clinic staff. Those patients who are referred to the study will be provided with an introductory letter and plain language statement in person during their clinic visit. Patients will be asked by the GP/clinic staff if they are willing to be contacted by the research team. If patients agree, the GP/clinic staff will provide the research team with the patient’s contact details.

The research assistant will contact patients who agreed to provide their contact details. Suitable and willing participants will be recruited by obtaining initial verbal consent. Written consent will be obtained at the time of the appointment with the practice pharmacist.

#### Baseline data collection

Baseline data will be collected by the research assistant using a structured questionnaire, either in person (at the clinic or the person’s home) or by telephone, and will include demographic information (age, sex, ethnicity, education, socioeconomic status, living arrangements etc.), health information (general health, health service use, health literacy [15] etc.), and medicines information (medication risk [14] adherence [16,17] etc.). The research assistant will then organize for the participant to meet the practice pharmacist for a long consultation.

#### Long patient consultation process

All participants will receive a 30–60 minute consultation with the pharmacist in a private room at the clinic (or a home visit if they prefer or are housebound) to perform a comprehensive medication review and identify medication-related problems (MRPs). Prior to the consultation, the pharmacist will discuss any health or medication-related issues with the GP or clinic staff, if needed. The pharmacist will also review participants’ general practice medical record (including progress notes, medication lists and pathology results) and dispensing histories if needed. The pharmacist will obtain written informed consent from the participant. In addition to reviewing the participant’s medication regimen, the pharmacist will assess medication adherence and knowledge. The pharmacist will provide counseling and education as needed on medication management and the use of medication devices, and reinforce lifestyle advice related to their health problems and medications. The pharmacist may provide the participant with a complete medication list and refer them to their community pharmacy for adherence aids (e.g. pill boxes, administration aids), if needed. Additionally, referral may be made to the GP or other health professionals as required. After the consultation, the pharmacist will write a short report outlining MRPs and recommendations, and provide this to the participant’s GP either electronically (via secure email or directly into the practice’s electronic medical record) or as a paper-based report, depending on the GP’s preference. The pharmacist may update the medication history within the practice’s medical record as needed. Following this, the pharmacist will discuss any issues with the GP, other staff and community pharmacist, if needed. Case conferencing may be organized where appropriate.

#### Monitoring and follow up

Participants will be followed up by the research assistant at three and six months either in the clinic or by telephone to collect data about implementation of pharmacist recommendations, resolution of MRPs identified by the practice pharmacist, participant’s medication adherence and participant’s general health and wellbeing.

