#### Sample size

Based on an expected average number of 2.5 MRPs per participant at baseline, an expected average reduction of 1 MRP (i.e. 40%) per participant with a within-participant standard deviation of 2.1 MRPs (assuming a correlation coefficient of 0.5), [18,19] a power of 80% and a two-tailed alpha of 0.05, the required sample size is 37 participants. Allowing for a dropout/loss to follow-up rate of 25%, at least 50 participants will be recruited. This was calculated using PS Power and Sample Size Calculations (Version 3.0, Dupont & Plummer, 2009).

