### Outcomes

#### Outcomes of long patient consultations

##### Medication-related problems

The primary outcome of the long consultations will be the number of MRPs identified by practice pharmacists and the number of identified MRPs that are resolved as a result of the pharmacists’ interventions. The number of MRPs, number of recommendations made by the pharmacists and the number of recommendations accepted/implemented will be recorded and determined by chart audit and/or patient interview, conducted by a research assistant. The types of problems will be categorized by the research team according to the criteria described by Strand et al [21]. The severity of the MRPs and the likely consequences if they had not been addressed will be assessed by an expert panel using a risk classification system [22].

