### Data analysis

Data will be entered into the Statistical Package for Social Sciences (SPSS) for Windows Version 19.0 (IBM, New York, USA) and analyzed using standard descriptive methods. Bivariate analysis will be performed between pre- and post-intervention data, using paired t-tests for continuous variables, McNemar chi-square tests for categorical variables, and Wilcoxon matched-pairs signed-ranks tests for ordinal variables. Comparisons between practices may be done using repeated measures analysis of variance (ANOVA). Binary logistic regression may be performed to identify independent predictors of having medication-related problems and effects on adherence and other outcomes.

Qualitative data management will be facilitated using NVivo® (Version 9, Qualitative Solutions & Research International, Melbourne, Vic). Interview transcripts will be read by two independent researchers and coded for emergent themes. Any discrepancies will be discussed and sorted in team meetings in the presence of a third researcher. A framework approach may be utilized whereby a thematic framework, based on *a priori* issues, will be applied to the data [26]. This will allow data to be easily indexed and charted, thus aiding subsequent interpretation.

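### Follow-up tracks only the medication-related problems listed at the consultation, so the change can only be zero or a fall; the sample size assumes two separate counts

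*Protocol article*

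**What the plan says.** Under *Long patient consultation process*, the pharmacist finds MRPs in a single 30–60 minute review.

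Under *Monitoring and follow up* for the long consultations, "Participants will be followed up by the research assistant at three and six months either in the clinic or by telephone". On MRPs, what is collected then is "resolution of MRPs identified by the practice pharmacist", together with implementation of the recommendations.

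Under *Outcomes – Medication-related problems*, the primary outcome is the number of MRPs identified and "the number of identified MRPs that are resolved as a result of the pharmacists’ interventions". The counts are to be "determined by chart audit and/or patient interview, conducted by a research assistant", with no time point attached.

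Under *Sample size*, the study is planned on a baseline mean of 2.5 MRPs and "an expected average reduction of 1 MRP (i.e. 40%) per participant with a within-participant standard deviation of 2.1 MRPs", with correlation 0.5, 80% power and two-sided alpha 0.05. This gives 37 participants, and at least 50 after 25% loss.

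Under *Data analysis*, "Bivariate analysis will be performed between pre- and post-intervention data, using paired t-tests for continuous variables". The section does not say which variables these tests apply to.

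**The concern.** A mean reduction with a standard deviation and a pre-post correlation describes a quantity measured afresh on two occasions, free to go up or down. The follow-up and outcome sections describe something else: a list drawn up once, whose items are then marked resolved or not. If the later count is the list minus its resolved items, no participant can get worse, and any MRP that arises after the consultation, including one arising from a change in medicines, goes unseen.

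Two things are at stake. First, a significant paired test could be reported as showing that the service reduces MRPs, when a modest amount of recorded resolution would be enough to produce it. Second, the stated power belongs to a different quantity from the one collected. The *Limitations* section admits the lack of a concurrent control group, but not that the outcome can move in only one direction.

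**Working it through.** **1. The plan's own figure.** Inputs from *Sample size*: mean difference 1, SD 2.1, correlation 0.5, two-sided alpha 0.05, power 80%. If 2.1 is the SD on each occasion, the SD of the difference is 2.1 × √(2 × (1 − 0.5)) = 2.1, so either reading gives the same value. With the noncentral t distribution, n = 36 gives 79.3% power and n = 37 gives 80.5%. Then 37 / (1 − 0.25) is 49.3, hence 50. Both stated figures reproduce, so a paired comparison of MRP counts is what was sized.

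**2. How little resolution is enough.** Let D be the number of listed MRPs resolved per participant, so D ≥ 0. In a t-test of mean D against zero with 37 participants:
- 3 participants with one resolved MRP each: t = 1.78, p = 0.083.
- 4 participants with one resolved MRP each: t = 2.09, p = 0.044.

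The expected total is 37 × 2.5 = 92.5 MRPs, so four are about 4%.

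**3. Rejection rate by resolution rate.** The resolution rates and the shape of the baseline distribution are assumptions. Baseline counts are negative binomial with mean 2.5 and SD 2.1, there are 37 participants, and each setting has 40,000 simulated trials.

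| MRPs resolved | Independent resolution | Within-participant ICC 0.2 | ICC 0.5 |
|---|---|---|---|
| 5% | 57% | 28% | 10% |
| 10% | 94% | 79% | 49% |
| 15% | over 99% | 96% | 81% |
| 20% | about 100% | 99% | 95% |
| 40% | about 100% | about 100% | about 100% |

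A Poisson baseline with independent resolution gives 60% at 5% and 96% at 10%. At 1% resolution the rejection rate is about 1%. If each participant's MRPs all resolve or none do (ICC 1), it is 16% at 10%, 43% at 15%, 69% at 20% and 99.5% at 40%.

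For contrast, suppose all MRPs were recounted and new ones arose as often as old ones resolved. The same test then rejects about 5% of the time or less.

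**4. Variance inputs at the planned 40%.** Write p for the resolution rate, V = 2.1² = 4.41 for the baseline variance and μ = 2.5 for the mean. The mean squared count is 4.41 + 2.5² = 10.66.
- Independent resolution: Var(D) = p²V + p(1 − p)μ = 0.16 × 4.41 + 0.24 × 2.5 = 1.306, so the SD is 1.14. The variance of the remaining count is 0.36 × 4.41 + 0.24 × 2.5 = 2.188. The pre-post correlation is (0.6 × 4.41) / (2.1 × √2.188) = 0.85.
- All-or-nothing resolution: Var(D) = 0.16 × 4.41 + 0.24 × 10.66 = 3.264, so the SD is 1.81. The variance of the remaining count is 0.36 × 4.41 + 0.24 × 10.66 = 4.146. The correlation is 2.646 / (2.1 × √4.146) = 0.62.

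Under these assumptions, even the most extreme clustering does not reach the plan's 2.1 and 0.5. By the formula of step 1, 80% power for a mean fall of 1 would need 13 participants with SD 1.14 and 28 with SD 1.81, both below 37.

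**5. Precision of the proportion resolved.** With 92.5 MRPs and p = 0.4, the 95% half-width is 1.96 × √(0.24 / 92.5) = 10.0 percentage points. With ICC 0.2, the design effect for unequal cluster sizes is 1 + (10.66/2.5 − 1) × 0.2 = 1.65, and the half-width is 10.0 × √1.65 = 12.8 points.

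**The case against.** Several points on the other side have weight.

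- **The test can fail.** A reader might infer that the paired test is bound to succeed. The figures do not support that: three of 37 participants with one resolved MRP each is not significant, and at 5% resolution the test misses about 43% of the time even when MRPs resolve independently. Strong clustering lowers rejection further. What stands is that the test cannot favour harm and is close to certain to reject at resolution rates well short of the planned 40%.
- **The outcome is qualified.** The primary outcome counts MRPs resolved through the pharmacist's intervention. A reader might infer that any background resolution would count, but as worded it should not. Whether a research assistant can make that attribution without a control group is a separate question. The qualification does not change the one-way nature of the count.
- **A recount is not excluded.** The outcome section has the number of MRPs determined by chart audit or interview, which could be read as a second count, and a condensed article may omit one. The absence of a recount is therefore inferred. The follow-up section, however, confines itself to MRPs already identified.
- **The variable is not named.** *Data analysis* does not assign the paired t-test to MRPs. The link comes from the sample size section, whose figures reproduce as a paired t-test.
- **The study is not underpowered.** This is correct: on the tracked outcome the plan's variance inputs are conservative.

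**Conclusion.** The point holds as a mismatch within the article. The follow-up and outcome sections describe tracking of a fixed list; the sample size section describes a paired reduction between two free counts; and the paired t-tests appear to be the matching analysis. On the tracked outcome, rejecting zero is near-automatic and uninformative once roughly 10% to 15% of MRPs are recorded as resolved, although it can be missed when resolution is very low or strongly clustered. The planning SD, correlation and 80% power do not describe this outcome.

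These sizes rest on the plan's mean of 2.5 and SD of 2.1, on 37 analysed participants, and on the assumed resolution rates and clustering. The one-way nature of the change depends on none of those figures, only on reading the follow-up as tracking. The stated outcome can still be reported validly as a description of what was found and resolved. What it cannot support is a claim of net reduction.

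**What to change.** - Do not test the tracked MRP count against zero, and do not call the result a net reduction in MRPs.
- Make the primary estimate the proportion of identified MRPs resolved by 6 months, alongside the mean number resolved per participant. Give a 95% confidence interval that allows for clustering within participant (GEE or a participant-level bootstrap).
- Report the number identified descriptively.
- Restate the sample size as precision: 37 participants, with about 92 MRPs, give roughly ±10 to ±13 percentage points around 40% for a within-participant ICC of 0 to 0.2. Treat 40% as a planning assumption, not as a benchmark for success.

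This needs rewording of three paragraphs and no extra patients or data. The price is that the power statement becomes a precision statement and the claim becomes descriptive.

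If a net reduction is the intended claim, the plan would instead need a recount of all MRPs, new ones included, by the same review method at follow-up. That would fit the paired comparison the study was sized for, but it costs extra pharmacist time.

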#### Sample size

Based on an expected average number of 2.5 MRPs per participant at baseline, an expected average reduction of 1 MRP (i.e. 40%) per participant with a within-participant standard deviation of 2.1 MRPs (assuming a correlation coefficient of 0.5), [18,19] a power of 80% and a two-tailed alpha of 0.05, the required sample size is 37 participants. Allowing for a dropout/loss to follow-up rate of 25%, at least 50 participants will be recruited. This was calculated using PS Power and Sample Size Calculations (Version 3.0, Dupont & Plummer, 2009).

#### Short patient consultation

Patients with potential medication issues (e.g. nonadherence, newly prescribed medicines) who do not require a comprehensive review of their complete medication regimen may receive a short consultation with the pharmacist. Data will be collected about these consultations, but the patients will not be consented for the study (no personal or identifying data will be collected). Referrals may be made by GPs or clinic staff, or patients may self-refer. The short patient consultation will last 15–30 minutes and provides an opportunity for the pharmacist to provide brief education and counseling on specific needs or answer questions. Short patient consultations will only be undertaken in the clinic. After the consultation, the pharmacist will write brief notes directly into the electronic medical record, and update records as needed. Examples of services to be provided in these consultations include: new medication counseling, adherence assessment, assessment of and education on device technique (e.g. using asthma inhalers), and provision of a medication list. Patient satisfaction will be assessed by an anonymous questionnaire to be given to each patient by the pharmacist along with a reply-paid envelope addressed to the researchers.

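### An earlier short consultation with the study's own pharmacist is neither an exclusion nor a recorded variable, so some long-consultation baselines may not be pre-intervention

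*Protocol article*

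**What the plan says.** All references are to the protocol article.

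- **Concurrent delivery.** Under Intervention: "A practice pharmacist will be co-located in each of the study clinics for at least eight hours per week for six months". The same pharmacist's tasks include both long and short consultations.
- **Who enters the long cohort.** Meeting a single inclusion criterion is enough for referral to be considered. One criterion is a general risk category that gives adherence issues as an example.
- **Who gets a short consultation.** Patients with a potential medication issue, with nonadherence as an example, who do not need a full review. Patients may refer themselves. The visit can include adherence assessment, counselling and a medication list.
- **What is kept from short consultations.** "Data will be collected about these consultations, but the patients will not be consented for the study (no personal or identifying data will be collected". The pharmacist also writes notes into the patient's electronic medical record.
- **What is excluded.** The only exclusion tied to an earlier medication service is: "Have had a HMR in the previous 12 months with no subsequent significant change in clinical status or medication regimen".
- **How change is measured.** Adherence is taken at baseline and again at three and six months. Data analysis compares pre with post by paired tests. The Discussion relies on participants acting as their own controls.

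**The concern.** The design has no control group, so the baseline value carries the whole inference. It has to be taken before the intervention starts. A patient can see the practice pharmacist briefly, receive adherence counselling and a medication list, and later be referred for a long consultation. That patient can satisfy the inclusion criteria and meet no exclusion. The baseline adherence score then follows contact with the study pharmacist, and part of the change under study may already have happened.

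For MRPs, a problem fixed at the short visit is missing from the list drawn up at the long visit, which lowers the baseline count. The Limitations section names the missing control group and the non-random sampling, but not this route. If the overlap is not recorded, the analysis cannot show whether it was trivial or common.

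**Working it through.** **1. Inputs (Sample size section).** Baseline: "expected average number of 2.5 MRPs per participant at baseline". Effect: "an expected average reduction of 1 MRP (i.e. 40%) per participant"; check, 1/2.5 = 40%. Spread: "within-participant standard deviation of 2.1 MRPs (assuming a correlation coefficient of 0.5", read here as the SD of the paired difference. Error rates and result: "a power of 80% and a two-tailed alpha of 0.05, the required sample size is 37 participants". Attrition: "Allowing for a dropout/loss to follow-up rate of 25%, at least 50 participants will be recruited".

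**2. Reproducing the plan's figures.** For a paired t-test, n = (t₀.₉₇₅ + t₀.₈₀)² × SD²/δ² with n − 1 degrees of freedom. With SD = 2.1 and δ = 1, iteration gives 36.6, so 37. Exact power from the noncentral t distribution at n = 37 is 0.805. Attrition: 37/(1 − 0.25) = 49.3, so 50. Both stated figures hold.

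**3. What prior contact could do to the MRP comparison.** Two quantities are needed, and the article gives neither, so both are assumptions:

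- f, the share of long-cohort participants with an earlier short consultation;
- c, the fraction of the planned 1-MRP change already used up in those participants.

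If prior contact acts only by reducing the change, the mean change becomes δ = 1 − f × c. Power then follows from the noncentrality δ × √37/2.1, with SD kept at 2.1. For example, f = 20% and c = 0.5 give δ = 0.90 and noncentrality 0.90 × 6.083/2.1 = 2.61, hence power 0.718.

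| f | c = 0.25 | c = 0.5 | c = 1 |
|---|---|---|---|
| 5% | 0.795 | 0.785 | 0.764 |
| 10% | 0.785 | 0.764 | 0.718 |
| 20% | 0.764 | 0.718 | 0.616 |
| 30% | 0.741 | 0.669 | 0.505 |

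While f × c is at most 0.05, the loss is about 4 points or less (0.805 to 0.764). At f = 20%, restoring 80% power would take 45 evaluable participants (45/0.75 = 60 recruited) if c = 0.5, or 57 (57/0.75 = 76) if c = 1.

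**4. Adherence.** The article gives no planning effect or SD for adherence, so no power can be computed. Under the same two assumptions its mean change would shrink by the same factor, 1 − f × c.

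**5. When the exclusion is applied.** If previously seen patients are screened out before enrolment, the target stays at 37/50. If they are dropped after 50 have been recruited, the evaluable number is 50 × 0.75 × (1 − f). At f = 10% this is 33.75 (33 used; power about 0.76). At f = 20% it is 30 (power about 0.71).

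**The case against.** Several points count against a stronger version, and most of them stand.

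- **Detectability.** A reader might infer from the absence of identifiers that overlap could never be found. The article does not support that. The pharmacist writes short-consultation notes into the medical record and reviews that record, progress notes included, before the long consultation. A research assistant may also audit charts. The quoted sentence limits only the research data. What remains is that neither the review nor the audit is said to capture prior contact: the exposure is unrecorded, not undetectable.
- **Different target groups.** Short consultations are meant for patients who do not need a comprehensive review, while the long cohort is at raised risk of MRPs. This should limit overlap. It does not rule it out, because no rule bars a later long consultation and the example reasons coincide.
- **Direction for MRPs.** A reader might infer a sure dilution of the primary outcome. That outcome counts problems identified at the long consultation and how many of those are resolved. Anything on the list is unresolved at that point, so its resolution is not carried over. A short visit could also bring problems to light and raise the later count. This objection stands in full.
- **Total loss of effect.** The c = 1 column assumes that a 15–30 minute visit on a specific need uses up all the benefit of a 30–60 minute full review. Nothing in the article supports that.
- **The HMR exclusion.** The article gives no reason for it, so it cannot be read as the authors acknowledging carry-over.
- **Condensation.** A single questionnaire item may sit in a fuller protocol. This weakens the recording half of the point. It does not remove the other half, because the article sets out its exclusion criteria and this contact is not among them.
- **Aim and conceded limits.** The study tests a multifaceted role and admits weak internal validity. Even so, the long-consultation cohort has its own outcomes and sample size, which rest on a valid baseline.

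**Conclusion.** The gap is real and moderate. Earlier contact with the study's own pharmacist is not excluded and not described as recorded, so for an unknown share of participants the baseline may follow part of the intervention. Attenuation is plausible for adherence. For MRPs the count available at baseline may be lower, but the direction of bias is not established.

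The stated 37 and 50 are correct, and this point does not show the study to be underpowered. If prior contact does attenuate the change, power at n = 37 would be about 0.76 (10% overlap, half the effect used up), 0.72 (20%, half) or, as a worst case, 0.62 (20%, all). These figures rest on assumed values of f and c and an unchanged SD of 2.1. A reader might also infer that the problem grows as the six months pass; that is reasonable, but the article gives nothing to test it with.

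**What to change.** At baseline, the research assistant asks whether the patient has already had a consultation with the practice pharmacist (yes/no, date). The answer is confirmed in the medical record, where the short-consultation notes are written. Then fix one of two rules in advance:

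1. exclude patients with such contact before enrolment, beside the HMR exclusion, which leaves the 37/50 target unchanged; or
2. keep them, and prespecify the pre-post adherence and MRP analyses with and without them.

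The cost is one questionnaire item, a chart check and one line of eligibility or analysis text. A few referred patients may not count towards the 50. No identifiers need to be added to the short-consultation data, so its consent arrangement is untouched. The choice should be made before recruitment, since dropping patients afterwards costs power.
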